**Fig. 1 fig1:**
[figure not shown]
Theoretical model of impact of PTSD symptoms on firearm storage practices.

Given that greater PTSD symptoms are associated with greater likelihood of non-secure firearm storage practices and existing LMSC interventions, namely PSG, demonstrate diminished efficacy in the setting of elevated PTSD symptoms, LMSC needs to be adapted for use in PTSD populations. The lack of evidence-based approaches for LMSC among individuals with PTSD likely contributes to gaps in care. In one study of 339 clinical psychologists, only 15% reported providing firearm-specific LMSC to their patients with PTSD [30]. In response, we developed an adaptation of PSG, termed Project Safe Guard-Trauma (PSG-T), designed for use with individuals who have PTSD to promote secure firearm storage practices, thereby reducing the risk of firearm-related harms such as suicide. PSG-T extends the MI practices demonstrated to be effective in PSG by exploring and addressing, including with psychoeducation, the potential functional link between trauma exposure and PTSD symptoms with firearm storage practices.

This paper describes the design, methodology, and protocol of an RCT examining the efficacy of PSG-T compared with PSG among firearm-owning individuals who screen positive for PTSD related to a victimization trauma (e.g., physical assault, sexual assault, combat, captivity). The overarching goal of the study is to expand the applicability of LMSC across at-risk populations, including individuals with PTSD for whom existing interventions demonstrate diminished efficacy. Secondary objectives are to evaluate a potential mechanism of change and heterogeneity of treatment effects (HTEs).

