#### Power

3.9.5

This study is powered according to the standardized effect size, Cohen's h, of the primary endpoint without considering correlations between longitudinal measures, which will provide a larger (more conservative) sample size estimate than if the study was powered based on the longitudinal correlation estimate in a GLMM [51]. Cohen's h is the standardized effect size for the between-group difference in proportions and is not affected by control group proportions [51,52]. Based on our preliminary result of the proportion of new uses of firearm locking devices in the intervention group (PSG-T, 30% = 55%–25%) and the control group (11.5% = 39%–27.5%), we calculated a Cohen's h of 0.47. A sample size of 150 (75 in each group) produces 80% power (α = 0.05) to detect a Cohen's h of 0.47 in measuring the between-group differences of proportions of reported new secure firearm storage behaviors. The proposed sample size of *N* = 168 participants (84 in each group) allows us to have >80% statistical power for the primary analysis and will yield 80% power to detect any subgroup-specific effect or standardized secondary outcomes of 0.47 or greater between PSG-T and control. The power will be at least 60% if the standardized subgroup-specific effect size is at least 0.35.

We used Monte Carlo simulation with 1000 replications to assess the power of *N* = 168 for the secondary outcomes, namely the mediation analysis of the PTSD-World in the PSG-T effect to increase knowledge, intentions, and behaviors regarding safe firearm storage practices [53]. Assuming the outcome standard deviation is 0.5, direct effect of PSG-T on PTSD is 0.6 and direct effect of PTSD on outcomes is 0.5, and the standard deviation is 1.3 for PTSD-World from Sexton et al. [54], a sample size of 168 allows us to detect a mediation effect of 0.30 (in Cohen's h scale) with 86 % power (α = 0.05).

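### The stated subgroup power (80% at 0.47, at least 60% at 0.35) rests on nearly the full sample and fails for subgroups of ordinary size

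*Protocol article*

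**What the plan says.** Section 3.9.5 (Power) of the protocol article derives its effect size from 30% new use of locking devices with PSG-T against "the control group (11.5% = 39%–27.5"%) and reports: "we calculated a Cohen's h of 0.47". It then states: "A sample size of 150 (75 in each group) produces 80% power" at that effect size. The trial enrols more than this: "The proposed sample size of *N* = 168 participants (84 in each group").

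From the enrolled number it draws two subgroup statements. The first is that this sample "will yield 80% power to detect any subgroup-specific effect or standardized secondary outcomes of 0.47 or greater between PSG-T and control". The second is: "The power will be at least 60% if the standardized subgroup-specific effect size is at least 0.35". Neither gives a subgroup, a subgroup size or an assumed prevalence. The section also says that its figures leave longitudinal correlation out.

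Subgroup effects matter to the stated aims. The Introduction says: "Secondary objectives are to evaluate a potential mechanism of change and heterogeneity of treatment effects (HTEs"). Section 3.9.4 (Missing data) puts missing primary outcomes at 6 months at no more than 10%.

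**The concern.** The section is at odds with itself. It needs 75 per group for 80% power at 0.47, has 84 per group in total, and then promises the same power at the same effect size inside any subgroup. Few subgroups would hold 75 of the 84 participants in each arm.

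Heterogeneity is a declared secondary objective, and the rationale for PSG-T is itself a moderation finding from the earlier PSG trial. Readers may therefore rely on these sentences when they interpret subgroup results. A non-significant result believed to have 80% power invites the conclusion that there is no effect in that subgroup. The same result at 40–60% power says little.

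**Working it through.** **Inputs.** From section 3.9.5: proportions 30% and 11.5%, h = 0.47 and 0.35, alpha 0.05, 75 and 84 per group. From section 3.5: equal allocation. From section 3.9.4: at most 10% missing, so 84 × 0.9 = 75.6 per arm. Sidedness is not stated. Two-sided is taken because it reproduces the 75 per group, whereas one-sided alpha would give 89% power at that size. Subgroup shares of one half and one third are assumptions, with both arms split alike.

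**1. Reproducing the plan's figures.**
- Cohen's h = 2·asin(√0.30) − 2·asin(√0.115) = 1.159 − 0.692 = 0.467, which rounds to the stated 0.47.
- The two-proportion sample size (pooled variance, no continuity correction) for 30% against 11.5% is 75 per group, with 80.4% power. This matches.
- On the h scale, power = Φ(h·√(n/2) − 1.96). With n = 75 and h = 0.47: Φ(2.878 − 1.96) = 82.1%.

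**2. Whole-trial power.**
- n = 84: Φ(3.046 − 1.96) = 86.1% at 0.47; Φ(2.268 − 1.96) = 62.1% at 0.35.
- n = 75.6: 82.4% at 0.47; 57.6% at 0.35.

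The stated 80% and 60% are therefore what the full or nearly full sample delivers.

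**3. Subgroup size that the claims require.** n per arm = 2·((1.960 + z)/h)², with z = 0.842 for 80% power and 0.253 for 60%.
- 80% at 0.47: 2·(2.802/0.47)² = 71.1, so 72 per arm. The share is 71.1/84 = 85% of participants, or 71.1/75.6 = 94% with 10% missing (72/75.6 = 95% after rounding up).
- 60% at 0.35: 2·(2.213/0.35)² = 80.0 per arm. The share is 80/84 = 95%. With 10% missing, 80 exceeds the 75.6 available.
- On the article's own count of 75 per group, the 0.47 claim would need 75/84 = 89% of participants.

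**4. Power in smaller subgroups.**

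| Assumed share | Missing | n per arm | Power at 0.47 | Power at 0.35 |
|---|---|---|---|---|
| One half | 0% | 42 | 57.7% | 36.1% |
| One half | 10% | 37.8 | 53.3% | 33.1% |
| One third | 0% | 28 | 42.0% | 25.8% |
| One third | 10% | 25.2 | 38.5% | 23.7% |

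**5. Effect detectable with 80% power in a half-size subgroup.** 2.802·√(2/n) = 0.61 for n = 42 and 0.64 for n = 37.8 (0.65 if 75.6 is first rounded down to 75, giving n = 37.5).

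**6. Side calculation: interaction.** For a difference of 0.47 between the effects in two equal halves, power = Φ(0.47/√(4/n) − 1.96), with n per arm in each half. This gives 33% for n = 42 and 30% for n = 37.8.

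**The case against.** The strongest defence is that the figures are conservative by design. They ignore longitudinal correlation, while section 3.9.1 plans a repeated-measures model adjusted for the baseline score, so real power may be higher. This stands as a reason to label the figures above as single-time-point figures. It does not rescue the claims. Even with complete data, a half-size subgroup would need the variance cut by about 41% (1 − 42/71.1) to reach 80% at 0.47, and the article claims no such gain. One-sided alpha does not help either: it fails to reproduce 75 per group, and a half-size subgroup would still have only about 70% and 48%.

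It is also fair to say that subgroup definitions and the test for heterogeneity belong in the full protocol or SAP, and their absence here is not criticised. The point rests on numerical statements that the article does make, and a later document cannot make them true for subgroups in general.

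Section 3.9.3 promises caution over secondary analyses, but on grounds of multiplicity. It does not address overstated power.

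Three stronger readings are tempting and are not supported:
- A reader might infer that the claims hold only if the subgroup is the whole trial. In fact about 85% of participants suffices at 0.47 and about 95% at 0.35 with complete data. The 10% loss is a stated ceiling, and the 0.35 claim survives a loss of about 5% in the whole sample.
- A reader might infer that heterogeneity will be judged by comparing significance between subgroups. The article describes no such comparison and does not rule out an interaction test.
- A reader might infer that the sample size is inadequate. Primary power on the h scale is 82–86%.

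**Conclusion.** The two subgroup power statements are wrong as written and should be corrected. They apply near-full-sample numbers to subgroups of unspecified size. The shortfall is material for ordinary splits: in a half-size subgroup, about 53–58% in place of 80%, and 33–36% in place of at least 60%. In a one-third subgroup the figures are about 38–42% and 24–26%. These results assume a two-sided 5% test, a single time point, equal allocation within the subgroup and 0–10% missing data; the subgroup shares are illustrative.

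This is a fault in what the article claims and does not threaten the design. The sample size, primary endpoint and primary analysis are unaffected, as is the 0.47 statement for full-sample secondary outcomes.

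**What to change.** In section 3.9.5, delete both subgroup power claims. Alternatively, restate each with an assumed subgroup fraction and the power that follows, marked as a single-time-point figure (for example, one half: about 53–58% at 0.47 and 33–36% at 0.35, with about 0.61–0.65 detectable at 80% power). Say that subgroup and heterogeneity results are not powered at 0.47. Keep the 0.47 statement for secondary outcomes in the full sample.

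Optionally, add that an interaction of 0.47 between two equal halves would have only about 30–33% power, noting that the equal split is assumed.

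The cost is the rewording of two sentences and less favourable stated figures. No new data, sample size change or design change is needed.

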#### Missing data

3.9.4

We expect minimal missingness (at most 10%) for the primary outcome at 6-month follow up, based on prior successes recruiting and retaining participants who report firearm ownership, and/or PTSD symptoms and the low missingness rate in prior related studies at 6-month follow-up [17,48]. Before the final analysis, missing data patterns will be assessed to determine if missingness is random/ignorable [49,50]. The logistic regression use in the primary analysis will use all available data and will adjust for covariates associated with missingness. Multiple imputation with chained equations for imputing outcomes missing at random will be considered. Patten-mixture models or sensitivity analysis will be considered if outcomes are not missing at random.

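### The mediation effect of 0.30 is a raw product of path coefficients, not a Cohen's h, and its 86% power assumes a residual SD, complete data and a linear outcome

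*Protocol article*

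**What the plan says.** Aim 2 (protocol article, section 2) asks whether negative cognitions about the world mediate the effect of PSG-T on three outcomes: storage behavior, knowledge and intentions. Its only power statement is the second paragraph of section 3.9.5: "We used Monte Carlo simulation with 1000 replications to assess the power of *N* = 168 for the secondary outcomes". All three outcomes are named there.

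The inputs are: "Assuming the outcome standard deviation is 0.5, direct effect of PSG-T on PTSD is 0.6 and direct effect of PTSD on outcomes is 0.5", with an SD of 1.3 for the world-cognitions mediator taken from a cited study. The result is that "a sample size of 168 allows us to detect a mediation effect of 0.30", described as being on the Cohen's h scale, with 86% power at α = 0.05.

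The first paragraph of the same section describes Cohen's h as the standardized effect size for a between-group difference in proportions and uses h = 0.47 for the primary endpoint. On missing data, section 3.9.4 says: "We expect minimal missingness (at most 10%) for the primary outcome at 6-month follow up".

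**The concern.** Three things in the statement do not fit what it is used for.

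- **Scale.** The effect is labelled with a measure that applies to proportions, yet no proportion enters it. A reader would naturally compare 0.30 with the primary h of 0.47 and conclude that the mediation analysis can detect a smaller effect on the same scale.
- **Meaning of the SD.** Whether 0.5 is the outcome's marginal or residual SD is not said. Only one of the two is compatible with the other inputs, and the size of 0.30 in SD units depends on it.
- **Coverage.** One figure, computed at the full 168, is offered for continuous outcomes and for a binary one alike.

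At stake is how an Aim 2 result is read. A null mediation finding, above all for storage behavior, could be taken as well powered on the strength of a figure that does not describe it. Neither the trial's sample size nor its primary analysis depends on this statement.

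**Working it through.** **Inputs** (section 3.9.5): arm-to-mediator path a = 0.6; mediator-to-outcome slope b = 0.5; mediator SD 1.3; outcome SD 0.5; 84 per arm; α = 0.05. My assumptions: two-sided test, no remaining direct effect of arm on outcome, normal errors, no missing data.

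**1. Where 0.30 comes from.** a × b = 0.6 × 0.5 = 0.30, in units of the outcome.

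**2. What a Cohen's h is.** h = 2·arcsin√p₁ − 2·arcsin√p₂. The primary figure reproduces: 2·arcsin√0.30 − 2·arcsin√0.115 = 0.467, stated as 0.47. Nothing of this form produces the mediation 0.30. The label matters: a plain two-arm comparison with h = 0.30 and 84 per arm has Φ(0.30/√(2/84) − 1.96) = Φ(1.944 − 1.96) ≈ 49% power, so a reader who takes it at face value is looking at a different quantity.

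**3. Which SD 0.5 can be.** The mediator alone contributes b × SD(M) = 0.5 × 1.3 = 0.65 to the outcome SD.
- As a marginal SD: 0.65 > 0.5, an implied correlation of 0.65/0.5 = 1.30. This is impossible without an offsetting direct effect.
- As a residual SD: outcome SD = √(0.5² + 0.65²) = √0.6725 = 0.82, which is coherent. Then 0.30/0.82 = 0.37 SD.

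**4. Reproducing 86% on the residual reading.** The slope is almost certain to be detected: its standard error is about 0.5/(1.3 × √168) = 0.030, so b/SE ≈ 17. The arm-to-mediator path therefore sets the power, and a two-sample t-test of that path (noncentral t) can be compared with a joint-significance simulation of both paths (60,000 runs).

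| Reading of 1.3 | N = 168: t-test / simulation | N = 151: t-test / simulation |
|---|---|---|
| Within-arm mediator SD | 84.5% / 84.5% | 80.4% / 80.1% |
| Total mediator SD (within-arm √(1.3² − 0.25 × 0.6²) = 1.265) | 86.4% / 86.3% | 82.5% / 82.7% |

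The protocol's 1000 replications carry a Monte Carlo standard error of √(0.86 × 0.14/1000) = 1.1 points, so 86% agrees with the N = 168 column.

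**5. Allowing for loss.** 168 × 0.9 = 151. The last column runs from 80% to 83%, or about 81% to 82% in the middle. The 10% is stated for the primary outcome; applying it to the mediation data, with complete cases only, is my assumption.

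**6. The binary outcome.** Improvement in storage is 0/1 with a logit link (section 3.9.1). On the linear scale a slope of 0.5 would mean 50 percentage points per mediator unit, or 2.6 × 50 = 130 points from one SD below the mean to one SD above, which a probability cannot do. So 0.5 needs another meaning there. As an illustration only, I took 0.5 as a log-odds slope and kept a = 0.6 and SD 1.3 (3,000 runs). With an improvement probability of 11.5% (the protocol's control figure) at the control-arm mean of the mediator, power is 68% at 168 and 62% at 151. With 30% it is 81% and 75%. The spread shows that this power depends on an event rate that the linear calculation does not contain.

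**The case against.** The best defence is that nothing is wrong with the 86%. A simulated mediation model is commonly specified by its residual SD; on that reading the inputs fit together and the figure reproduces. This stands.

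Two stronger readings are therefore tempting but unsupported. A reader might infer that 0.30 is unattainable under the stated inputs; that follows only if 0.5 is the marginal SD and there is no offsetting direct effect, and the text does not say that it is. A reader might also infer that 86% is overstated because a weaker mediator-to-outcome slope would give less power; but the protocol states 0.5, so a smaller slope is a different hypothesis and not a correction.

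On attrition, the defence says that 10% is given for the primary outcome only, that the mediator is also measured post-intervention and at 1 and 3 months (Table 2), and that multiple imputation will be considered (section 3.9.4). This stands as a reason to call 151 an assumption. Nor does the text tie 168 to attrition, although 150/0.9 = 167 suggests it. Even at 151, power stays at about the conventional 80%.

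Finally, the mediation analysis does not size the trial, section 3.9.3 promises caution with secondary analyses, and an article may leave simulation detail to the full protocol. That limits the weight of the point. It does not excuse a stated scale that contradicts the section's own definition, or a claim that explicitly extends to behaviors.

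**Conclusion.** The point holds in a limited form.

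- **Certain:** 0.30 is not on the Cohen's h scale as section 3.9.5 itself defines it, and it is not comparable with 0.47.
- **Unclear label:** 0.5 has to be a residual SD for the inputs to agree, barring an offsetting direct effect. The effect is then about 0.37 outcome SDs. The power hardly depends on this, because the arm-to-mediator path limits it.
- **Power:** 86% is right on the stated inputs with all 168 complete. It becomes about 81% to 82% at 151, a drop of 4 to 5 points from the stated figure, if the primary outcome's expected loss applies to the mediation data.
- **Coverage:** the figure describes a continuous outcome on a linear scale. It says nothing reliable about the binary storage outcome, for which the true power could be higher or lower than an unaided reading suggests, depending on the event rate and on what the slope means.

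**What to change.** In the second paragraph of section 3.9.5:

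1. Remove the reference to the Cohen's h scale and give the mediation effect as 0.30 in outcome units, about 0.37 outcome SDs.
2. Say that 0.5 is the residual outcome SD, and whether 1.3 is the within-arm or the total mediator SD.
3. Quote power at the number expected to be evaluable for mediation (about 81% to 82% if that is 151), with the assumed loss stated.
4. Either limit the statement to knowledge and intentions, or add a separate simulation for storage behavior with a logistic outcome model, a stated event rate and a slope on the log-odds scale.

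The cost is a short rerun, a few reworded sentences and a stated power 4 to 5 points lower. Sample size, design and the primary analysis are unaffected.

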## Discussion

4

This manuscript provided an overview of the methodology and protocol of an RCT that will examine the efficacy of PSG-T compared with PSG among firearm-owning adults who screen positive for PTSD related to a victimization trauma (e.g., physical assault, sexual assault, military combat) and who do not currently store all their firearms securely (e.g., unlocked and/or unloaded). Given that the non-secure storage of personally owned firearms is associated with elevated suicide risk for the firearm owner and others in the home, and given that the existing PSG intervention has demonstrated diminished efficacy for individuals with elevated PTSD symptoms, identifying a novel, PTSD-focused LMSC intervention has the potential to reduce firearm-related harms, including suicide. If PSG-T demonstrates success in prompting secure firearm storage beliefs and practices, then PSG-T will address a critical healthcare gap for at-risk individuals with PTSD.

### Consideration of alternative study designs

4.1

There are five primary study design considerations that warrant mention (see Table 3).

**Table 3 tbl3:** Considerations of alternative study designs.

Consideration	Decision and Rationale
**Inclusion Criteria: Positive PTSD Screen vs. PTSD Diagnosis**	We elected to screen for PTSD using the PC-PTSD-5, consistent with PTSD screening recommendations in the VA/DOD CPG [55]. We considered whether to include participants with a PTSD diagnosis using the reference standard Clinician-Administered PTSD Scale for DSM-5 (CAPS-5) [56]. We decided to select individuals who screen positive for PTSD using the total PC-PTSD-5 for three reasons: (1) the PC-PTSD-5 is considerably briefer and more feasible to administer in the context of study inclusion screening (i.e., 5 vs. 60+ minutes); (2) assessing for symptoms rather than diagnoses aligns with findings from our pilot data indicating that existing LMSC have diminished efficacy for individuals with elevations on the total PCL-5 score [57]; and (3) this approach will align with clinical operations within the DOD, Veterans Health Administration, and other healthcare systems that typically rely on screening instruments such as the PC-PTSD-5 to make treatment-planning decisions.
**Inclusion Criteria: PTSD Symptoms Related to a Victimization Trauma**	We are limiting the sample to individuals who screen positive for PTSD related to their experience of a victimization trauma—that is, those that are interpersonal in nature, such as physical assault, sexual assault, or combat. Individuals who experience other traumatic events, such as natural disasters (e.g., hurricanes) or motor vehicle accidents, are ineligible unless they have also experienced a victimization trauma for which they screen positive for PTSD. We considered whether to limit participation on this criterion. However, unpublished evidence from our group suggests that among individuals with a victimization trauma history (but not an accident or injury trauma history), PTSD symptoms are associated with non-secure firearm storage practices.
**Intervention: Control Condition**	We elected to use an active control (i.e., PSG) rather than an inactive or attention control (e.g., health and stress counseling as in the original PSG trial) for two primary reasons. This approach would ensure that all participants, all of whom report firearm ownership and the non-secure storage thereof, would receive at least the PSG intervention, which has demonstrated efficacy in prior trials (cf. beneficence). This approach would also provide an answer to the question: does PSG-T outperform PSG for individuals who screen positive for PTSD?
**Intervention: Inclusion of Crisis Response Planning**	We decided to include CRP. One concern was that the CRP intervention would introduce unnecessary heterogeneity into the study methodology. However, CRP is inert regarding the outcomes of interest (i.e., there is no LMSC component of CRP) and the administration of CRP is balanced across conditions. Furthermore, in many clinical care settings, LMSC would not be administered without some sort of safety planning intervention.
**Intervention: Distribution of Firearm Locking Devices**	We considered whether to provide participants with locking devices, such as cable locks. The initial PSG RCT was a 2x2 factorial design (i.e., LMSC vs. control, provision of cable locks vs, no cable locks), and findings indicated that the combination of LMSC and gun lock provision was not superior to either intervention alone [58]. This suggests that distributing cable locks does not enhance LMSC. Additionally, cable locks are the most affordable locking device and, therefore, would be an appropriate device to consider regarding future scalability. However, firearm owners cite cable locks as among the least preferable device [59] and there are knowledge gaps in proper cable lock use [60].

